## Trial design {8}

This study is a parallel group, evaluator-blinded, phase-II, single-center RCT [53]. Participants will be assigned to the intervention or active control group, with an equal (1:1) allocation ratio, based on stratified randomization. The study protocol is reported according to the SPIRIT (Standard Protocol Items: Recommendations for Interventional Trials) statement [54, 55]. Figure 1 gives a graphical overview of the described RCT. The study protocol, including the therapy intensity, practical organization of the therapy delivery, and duration of the assessments at each timepoint, was discussed with relevant stakeholders during online video-meetings to improve the feasibility of this RCT. The stakeholders that participated during these meetings were physiotherapists working in private practices across Flanders and children and adolescents with uCP and their parents.

**Fig. 1 Fig1:**
[figure not shown]
Flowchart of the described RCT based on the CONSORT guidelines [56]. Abbreviations: uCP = Unilateral cerebral palsy; MACS = Manual Ability Classification System; Baseline (T_0_) = Maximally 2 weeks before the start of the therapy; Post (T_1_) = Maximally 2 weeks after the therapy has ended; Follow-up (T_2_) = 6 months after the therapy has ended, within a time frame of 2 weeks

## Methods: participants, interventions, and outcomes

### Study setting {9}

Children and adolescents with uCP will be recruited across Flanders (Belgium) via the Cerebral Palsy Reference Centre of the University Hospitals Leuven, private pediatric physiotherapists and special needs education schools.

### Eligibility criteria {10}

Participants will be selected based on the following inclusion criteria: (1) diagnosis of predominantly spastic uCP; (2) aged 7 to 15 years old at the time of baseline assessment; (3) sufficient cooperation to comprehend and complete the test and therapy procedures; (4) minimal ability to actively grasp and hold an object with the more impaired hand (Modified House Functional Classification System (mHFCS) ≥ 4 [57]); and (5) having a confirmed impairment in tactile registration and/or tactile perception, as objectified using a clinical assessment battery (see eligibility screening). The study will not include children and adolescents who (1) received botulinum toxin-A injections six months prior to the baseline assessment; (2) underwent upper limb surgery one year prior to the baseline assessment; and (3) are unable to communicate in Dutch. Eligibility of the participants will be confirmed by the researchers based on an eligibility screening, which is described below.

### Who will take informed consent? {26a}

Parents and potential participants will be informed about the study protocol by giving an in-person explanation, supported with written information documents. Afterwards, written informed consent to participate in the eligibility screening will be obtained from the parents or legal caregiver. Children and adolescents will be asked to additionally sign the informed assent form. When a child or adolescent meets the eligibility criteria based on the screening, an additional written informed consent and assent form to participate in the intervention study will be completed by the parents or legal caregiver and participant, respectively. The explanation of the study and informed consent procedure will be performed by one of the researchers.

### Additional consent provisions for collection and use of participant data and biological specimens {26b}

N/a—The collected participant data will not be used in ancillary studies.

## Interventions

### Explanation for the choice of comparators {6b}

Within this RCT, we aim to investigate if a therapy approach focusing on somatosensation has a superior effect to improve sensorimotor upper limb function in children and adolescents with uCP who present with tactile impairments in the upper limb, compared to a dose-matched motor therapy. A dose-matched active comparator was selected to eliminate differences in therapy intensity between both groups.

### Intervention description {11a}

Participants in both groups will receive three sessions of 45 minutes upper limb therapy per week for a period of eight weeks, resulting in a total therapy duration of 18 hours. All therapy sessions will be performed by individual physiotherapists or occupational therapists who have experience working with children with CP. The participant/therapist ratio will be 1:1 for both therapy groups.

#### Somatosensory discrimination therapy

Participants in the intervention group will receive the Sense for Kids therapy, which is a highly structured intervention program for the upper limb that aims to improve different aspects of somatosensory function [58]. More specifically, the therapy includes graded practice of three components of somatosensation (i*.*e., component-based therapy): tactile object recognition, texture discrimination, and body position sense. Furthermore, it contains the repetitive practice of self-chosen activities of daily living during which attention is designated to the somatosensory features necessary for successful task performance (i.e., occupation-based therapy). The self-chosen activities will be determined based on the results of the Canadian Occupational Performance Measure (COPM) [59], as described below. The same principles of perceptual learning as described in previous studies [36, 37, 41, 58] will be applied, consisting of active exploration without vision, calibration with the less impaired hand and with vision, feedback on performance and method of exploration, anticipation trials, repetition, and progression from easier to more difficult tasks. Each therapy session will consist of 30 minutes of component-based therapy, during which at least two different components of somatosensation will be practiced. These components will be selected based on the somatosensory profile of the child. The remaining 15 minutes consist of occupation-based therapy, during which one or two activities of daily living will be performed. To assure the quality of the therapy, all therapists who will perform the Sense for Kids therapy will follow an instructional course organized by the researchers. A therapy manual and all necessary therapy materials are developed based on the ones adapted by McLean et al. [41, 58] and will be provided to the therapists. The therapy manual contains detailed information regarding therapy delivery, points of attention, and methods of progression.

#### Upper limb motor therapy

Participants in the control group will receive an equal amount of intensive upper limb motor therapy. During each session, they will perform 30 minutes of unimanual motor tasks and 15 minutes of bimanual goal-directed training. For the unimanual motor tasks, a therapy manual will be provided by the researchers. This manual is developed in a similar manner as the one developed by Klingels et al. [44] and contains general information regarding therapy provision (i.e., progression/regression and number of repetitions). The manual also includes specific exercises grouped according to commonly reported upper limb motor problems: grasping and releasing, forearm supination, active wrist extension, thumb movements, and fine motor skills. Relevant exercises will be selected on an individual basis considering the upper limb function of the child or adolescent. This selection will be made by the researchers in collaboration with the individual therapist of the participant, taking into account measures of upper limb function performed at baseline and available in the medical record of the participant. During each session, participants will perform exercises targeting at least two different categories of upper limb problems. The bimanual goal-directed training includes repetitive whole-task practice of self-chosen activities of daily living, which will be determined based on the results of the COPM. During each session, one or two different activities of daily living will be practiced. Selected motor learning principles will be implemented throughout the upper limb motor therapy, including repetitive whole-task practice, progressive increases of task difficulty, provision of external feedback on task performance, and task specificity [19, 60, 61].

### Criteria for discontinuing or modifying allocated interventions {11b}

N/a—The participant may voluntarily withdraw consent to participate for any reason at any time. The participant’s request to withdraw from the study will always be respected without prejudice or further consequences.

### Strategies to improve adherence to interventions {11c}

To evaluate compliance, therapists from both groups will be asked to record the frequency and duration of the effective therapy time and the executed exercises/activities. After the first week of intervention and halfway through the intervention period, parents and therapists will be contacted by one of the researchers to discuss the feasibility of the therapy and the progress the child has made.

Furthermore, for the intervention group, adherence of the therapists to the Sense for Kids therapy protocol will be scored using a fidelity checklist that contains all fundamental elements of the therapy and relevant implications regarding therapy receipt (Additional file 1) [58]. The fidelity checklist was audited by five researchers and clinicians who have experience with the provision of Sense for Kids therapy. Modifications were made to improve clarity of the necessary elements, include essential elements of occupational-based therapy and remove assessment items to confine the forms application to individual and subsequent Sense for Kids therapy sessions. Fidelity of three randomly selected therapy sessions of each participant will be assessed based on a video recording of the therapy session. All video recordings will be scored by an independent reviewer who has experience with the Sense for Kids therapy but is not involved in the provision of therapy within the scope of this study. Each criterion will be scored on a 4-point Likert scale and a percentage score will be computed to objectify adherence. A percentage score of 80% or higher will be considered as sufficient adherence to the therapy protocol.

### Relevant concomitant care permitted or prohibited during the trial {11d}

In agreement with the treating physician and physiotherapist of the children and adolescents, conventional physiotherapy and occupational therapy for the upper limb will be replaced by the intervention within this study during the course of the 8-week intervention period. Other usual care, such as the use of splints and night orthoses or physiotherapy for the trunk and lower limbs, can be continued throughout the course of the study. During the follow-up period conventional physiotherapy and occupational therapy for the upper limb will be continued again. Information regarding the upper limb therapy received six months before therapy commencement and during the follow-up period will be collected based on a questionnaire completed by the parents and individual physiotherapist of the child or adolescent. When a participant receives botulinum toxin-A injections or upper limb surgery during the course of this study, the participant will be excluded and no additional data will be collected.

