## Assignment of interventions: allocation

### Sequence generation {16a}

After enrollment and prior to the baseline assessment, participants will be assigned to the intervention or control group through randomization by minimization with an allocation ratio of 1:1. A minimization technique will be used to enhance homogeneity between both groups. To diminish allocation prediction, an additional random component of 80% probability will be implemented. The first participant, and in case the marginal totals are equal between both intervention groups, simple randomization will be performed. Participants will be stratified based on age (2 levels: < 11 years and ≥ 11 years), manual ability (3 MACS-levels: I, II, and III) and tactile impairment (2 levels: mild or moderate-severe – flowchart shown in Fig. 3).

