### Plans to promote participant retention and complete follow-up {18b}

To avoid dropouts due to practical considerations, the scheduling of therapy and assessment sessions will be adapted to the participant’s preferences where possible. Furthermore, one contact person will be appointed to coordinate the scheduling of therapy and assessments and to resolve any questions. Lastly, parents will be contacted after the first week of therapy and halfway the intervention period to discuss feasibility of the therapy and the progress the child has made. In case of deviations from the study protocol (e.g., missed therapy sessions due to illness), the assessments will still be scheduled as described above and the specific deviation will be noted.

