## Statistical methods

### Statistical methods for primary and secondary outcomes {20a}

All observations will be summarized as mean and standard deviation or median and interquartile range, according to the nature of the data. Baseline comparability between groups will be visually checked based on descriptive statistics. As the participants will be randomized to the intervention or control group, statistical testing of baseline differences will not be performed [108]. To study the time effects of the intervention and to allow for comparison between both groups, linear or generalized mixed models will be applied for the primary and secondary outcome measures. By using random effects, such models correct for the relation among repeated observations within subjects. An additional benefit of these models is that they provide a valid inference for missing values that are (completely) at random [109]. In case the data of an outcome measure is not normally distributed based on the Shapiro–Wilk test and/or visual inspection of the data distribution, transformations will be applied. The main endpoint will be to investigate if there is a difference in evolution of the AHA score over time between both groups. As such, interactions between therapy and time will be analyzed to test for differences in improvements over time between both groups (time*group interaction effect). When a significant interaction is identified, time trends will be tested in both therapy groups separately (time-effect). When the interaction is not significant, the main effect of time will be explored. Effect sizes for the full models will be further calculated using the Cohen’s partial η^2^ formula [partial η^2^ = (F × df_between_)/((F × df_between_) + df_within_)] [110]. Significant time trends will be further investigated with pairwise post hoc tests to compare individual time points (*T*_0_–*T*_1_, *T*_1_–*T*_2_, *T*_0_–*T*_2_). For the model of the primary outcome measure, the post hoc analysis will be Bonferroni corrected and the pairwise post hoc test for *T*_0_–*T*_2_ will be the primary outcome. For the models of secondary outcome measures, a false discovery rate with an adjusted *p*-value of 0.05 will be implemented. Effect sizes of these comparisons will be calculated using Cohen’s d formula [111]. For the second research objective, we will investigate predictive factors of therapy response. Both behavioral and neurological characteristics, i.e., somatosensory function at baseline, attentional functioning, and thalamic volume, will be included as covariates in the model for the primary outcome measure. All statistical analyses will be performed in SPSS Statistics for Windows. Level of significance will be set at 0.05, two-sided. When needed, adapted statistical techniques will be applied in close collaboration with Leuven Biostatistics and statistical Bioinformatics Centre (L-BioStat).

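### Stopping data collection after botulinum toxin-A or upper limb surgery discards primary outcomes of randomized children and could bias the 6-month comparison

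*Protocol article*

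**What the plan says.** The rule is in item {11d}, on concomitant care. A child who receives botulinum toxin-A or upper limb surgery "during the course of this study, the participant will be excluded and no additional data will be collected". The same item lets conventional upper limb therapy resume during follow-up and records it by questionnaire.

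Item {16a} places randomization early: "After enrollment and prior to the baseline assessment, participants will be assigned". The primary outcome is the change in AHA from T0 to T2 (Table 1), and T2 falls "6 months after the therapy has ended, within a time frame of 2 weeks" (Fig. 1 legend).

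The eligibility criteria bar the same treatments beforehand. They leave out children who "received botulinum toxin-A injections six months prior to the baseline assessment", or who had upper limb surgery in the year before it.

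For incomplete data, item {20a} relies on mixed models, on the ground that "they provide a valid inference for missing values that are (completely) at random". Item {20c} refers back to {20a}.

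For other departures, such as sessions missed through illness, item {18b} says that "the assessments will still be scheduled as described above and the specific deviation will be noted".

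**The concern.** A child excluded under {11d} has already been randomized, and the exposure is long: 8 weeks of therapy plus 6 months of follow-up, ending at the primary visit. Both treatments act on the measured limb, and one plausible reason for giving them is how that limb is doing after allocation. The trial's own hypothesis (Objectives {7}) is that bimanual performance keeps improving after somatosensory therapy but not after motor therapy. If so, hand function diverges between the arms in the very months when exclusion can occur, and so might the exclusions.

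If children with poorer change are removed more often from one arm, that arm's observed mean is too high. Loss from the motor arm would hide a benefit of somatosensory therapy; loss from the somatosensory arm would exaggerate it.

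This is not a detail that an analysis plan could settle. It is a positive instruction not to collect data, and no later analysis can restore a T2 score that was never taken.

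**Working it through.** **Inputs, from Sample size {14} and {20a}.** Target difference 5 AHA units; SD of change 5.5; effect size 0.9 (5/5.5 = 0.909); alpha 0.05 two-sided; power 0.80; 21 per group, raised to 25. The allowance is 4 of 25, or 16%, and each child lost is 1/25 = 4% of an arm. The documents give no rate, reason or arm split for the {11d} exclusions, so the rates and correlations below are assumptions.

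**The plan's own figure.** A two-sample t-test with effect size 0.9, two-sided alpha 0.05 and power 0.80 needs 20.39 per group, so 21. This reproduces the stated number. Power is 0.812 at 21 per group and 0.877 at 25. The sample size is not in question.

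**Shift in one arm's completer mean.** Let a fraction p be excluded, where the tendency to be excluded has correlation r with poor AHA change (both normal). The mean of those who remain rises by

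shift = r × 5.5 × φ(z_p) / (1 − p),

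with z_p the p-quantile of the standard normal and φ its density. For p = 0.16, z = −0.994 and φ(z) = 0.243, so at r = 1 the shift is 5.5 × 0.243 / 0.84 = 1.59.

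| r | 4% excluded | 8% | 16% |
|---|---|---|---|
| 0.3 | 0.15 | 0.27 | 0.48 |
| 0.5 | 0.25 | 0.44 | 0.80 |
| 1 (the lowest changes, exactly) | 0.49 | 0.89 | 1.59 |

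With loss in one arm only, the between-group difference moves by the same amount. Against the 5-unit target, 0.15/5 = 3% and 0.80/5 = 16%. The 1.59 units (32%) require perfect selection and the whole allowance of one arm spent on these two treatments.

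**Effect on the test.** Completer t-test, 25 randomized per arm, 40,000 simulated trials, r = 0.3 and 0.5. Bias is intervention minus control; power is for a true effect size of 0.9 favouring the intervention.

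- 16% lost from control, none from intervention: bias −0.48 and −0.80 units; type I error 0.060 and 0.079; power 0.77 and 0.72. With r = 0 and the same loss, power is 0.84.
- 16% against 4%: bias −0.32 and −0.54; type I error 0.054 and 0.063; power 0.79 and 0.77.
- 16% in both arms by the same mechanism, or r = 0: bias about zero; type I error about 0.05.

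**What the mixed model can do.** The figures above are for completers. The planned model can use AHA scores taken before the event, which removes the bias if the loss is missing at random given those scores. No AHA is scheduled between T1 and T2, so a decision driven by function in that interval may depend on values not observed. A child excluded before T1 contributes T0 at most.

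**The case against.** The rule is deliberate and coherent. The eligibility criteria bar the same treatments before baseline, and {11d} keeps their effect out of the T2 score. Continued measurement would change the question, because T2 would then include any effect of toxin or surgery. The natural reading of the rule is that only future collection stops, so T0 and often T1 stay in the model. Poor function or a disappointing response could well show in those scores, which is where missing at random is most credible. The sample size already allows for dropout.

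Much of this stands. The power loss is covered, the mixed model may remove part or all of the bias, and wanting an estimate free of later limb treatment is legitimate. But that calls for an analysis that sets post-event values to missing, not for leaving them uncollected. Measuring everyone permits both analyses; the present rule permits only one.

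Three stronger readings are tempting, and the documents support none of them.

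- A reader might infer that the exclusion is outcome-related and breaks the randomized comparison. No section says why, how often or in which arm these treatments would be given. That the loss could bias the result is as far as the text goes.
- A reader might take 1.6 units as the likely bias. It is an extreme bound.
- A reader might see {11d} as contradicting {11b} or {18b}. Item {11b} deals with stopping the allocated intervention and says "The participant may voluntarily withdraw consent to participate for any reason at any time"; a rule on other treatments belongs in {11d}. The example in {18b} is missed sessions, a different event. It shows only that the trial already keeps assessing children after other deviations.

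**Conclusion.** The point holds as a risk that the protocol creates for itself. Item {11d} discards primary outcomes of randomized children for a reason that could be linked to outcome and allocation, and it rules out an as-randomized analysis of them. The planned model protects only under missing at random given the AHA scores already taken.

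The size is unknown and may be nil. With 4% to 16% lost from one arm only and a correlation of 0.3 to 0.5, the completer difference moves by 0.15 to 0.80 AHA units. Loss spread over both arms gives less. This merits an amendment, but it does not show that the trial's result will be wrong.

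**What to change.** Amend {11d} so that a child who receives either treatment stays in the trial for data purposes: T1 and T2 assessments as scheduled, subject to consent, with the date and type of the event recorded. State that the primary analysis includes all children as randomized, and add a sensitivity analysis that sets values after the event to missing. Nothing in any child's care changes.

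The cost is a small amendment with matching consent wording, and a few more follow-up visits. The primary estimate would then include the effect of this later care, as it already does for conventional therapy resumed in follow-up. Recruitment may run until 30 June 2027 (Trial status), so an early amendment saves the most data; T2 visits already missed under the present rule cannot be recovered.
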